**Figure 3 F3:**
[figure not shown]
Bristol stool form classification diagram.

**Table 3 T3:** Bristol stool form classification scoring table.

Type	Form	Score
1	Separate hard lumps, like nuts, difficult to pass	1
2	Sausage-shaped but lumpy	2
3	Sausage-shaped with cracks on surface	3
4	Sausage or snake-shaped, smooth and soft	4
5	Soft blobs with clear edges, easy to pass	5
6	Fluffy pieces with ragged edges, mushy	6
7	Watery, no solid pieces	7

##### Bowel urgency

2.7.3.2

Bowel urgency reflects the temporal urgency for defecation following medication. The shortest daily response interval is recorded and quantified on a 0–3 scale: 0 = no urge/>3 h, 1 = ≤ 3 h, 2 = ≤ 2 h, 3 = ≤ 1 h. Assessment time points are baseline, Week 2, and Week 4.

##### Glucose and insulin metabolism parameters

2.7.3.3

Parameters include fasting blood glucose (FBG), 2-h postprandial glucose (PG2h), fasting C-peptide, fasting insulin (FINS), HOMA-IR, and insulin sensitivity index (ISI). Glucose profiles are obtained via continuous glucose monitoring, and glycated albumin (GA) is used for short-term glycemic control assessment. Assessments occur at baseline and Week 2, with glucose monitoring continued for 4 weeks. HOMA-IR = (FBG × FINS)/225; ISI = 1/(FBG × FINS).

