#### Diagnostic criteria for type 2 diabetes mellitus

2.3.1

The diagnosis of diabetes will follow World Health Organization (WHO) criteria (Puavilai et al., 1999; Kansagara et al., 2019). A diagnosis of T2DM will be made if any of the following criteria are satisfied:

(1) Fasting plasma glucose (FPG) ≥ 126 mg/dl (7.0 mmol/L) after an overnight fast of at least 8–14 h (venous or capillary);(2) 2-h postprandial venous plasma glucose ≥ 200 mg/dl (11.1 mmol/L);(3) 2-h postprandial capillary plasma glucose ≥ 220 mg/dl (12.2 mmol/L);(4) Random plasma glucose ≥ 200 mg/dl (11.1 mmol/L);(5) Glycated hemoglobin (HbA1c) ≥ 6.5%.

Borderline or inconclusive results should be repeated on a subsequent day. Typical hyperglycaemic symptoms (for example, polyuria, polydipsia, unexplained weight loss, or blurred vision) may support the diagnosis.

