#### Standard care (background therapy)

2.6.1

Background therapy follows international guideline recommendations and comprises standardized lifestyle counseling and medication management. Lifestyle counseling includes: dietary guidance with carbohydrates accounting for 45–60% of total daily energy intake and dietary fiber ≥25 g/day; at least 150 min/week of moderate-intensity aerobic activity (for example, brisk walking or cycling); and standardized education on disease management, medication adherence, and management of gastrointestinal symptoms to ensure consistency across participants (American Diabetes Association, 2024a,b).

Medication management principles are as follows:

Discontinue or avoid medications known to exacerbate gastrointestinal symptoms where clinically appropriate (e.g., stimulant laxatives or certain over-the-counter preparations);

In participants with inadequate glycaemic control, additional antihyperglycaemic agents (for example, SGLT2 inhibitors or DPP-4 inhibitors) may be added as clinically indicated, provided such additions are unlikely to aggravate gastrointestinal function; adjustments will follow current guideline recommendations and be documented;

Concomitant treatment for chronic conditions (e.g., antihypertensives for hypertension or secondary prevention therapies for coronary artery disease) will be maintained but clinicians should avoid introducing agents known to provoke GI intolerance when alternatives are available.

Metformin dosing will follow a “start low, escalate gradually” regimen: initial dose 500 mg administered with meals twice daily; dose titration will proceed weekly guided by fasting blood glucose (target 4.4–7.0 mmol/L), with a maximum dose up to 2,000 mg/day or the participant's maximal tolerated dose. Dose adjustments and all concomitant medications will be supervised and recorded by study physicians. In the event of severe, poorly tolerated diarrhea (e.g., ≥5 bowel motions per day with clinical signs of dehydration), metformin will be withheld or adjusted and symptomatic therapy provided (e.g., diosmectite); severe events will be managed according to the study Serious Adverse Event (SAE)—defined per the Common Terminology Criteria for Adverse Events (CTCAE) as any adverse event resulting in death, life-threatening illness, hospitalization, persistent disability, or requiring immediate emergency intervention—procedure and continue to be followed up (Rena et al., 2013).

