### Statistical methods

2.10

All data will be managed according to GCP guidelines for clinical trials. Two independent researchers will perform double data entry for all variables, including bowel urgency scores, glucose and insulin metabolism markers, serum inflammatory markers, and safety parameters. Cross-verification is mandatory, and the database will be locked without authorization.

Statistical analyses will be performed by blinded biostatisticians using SAS 9.4 and R 4.2.1. Two analysis sets will be applied: the intention-to-treat (ITT) set includes all randomized participants, and the per-protocol (PP) set includes participants completing ≥80% of the treatment course without major protocol violations, for sensitivity analysis.

Baseline characteristics will be summarized by group. Continuous variables are assessed for normality using the Shapiro–Wilk test: normally distributed variables are presented as mean ± SD, non-normal as median [IQR]; variance homogeneity is assessed via Levene's test. Categorical variables are expressed as counts (*n*) and percentages (%). Between-group comparisons: independent *t*-test or Mann–Whitney *U*-test for continuous variables, Pearson χ^2^ or Fisher's exact test for categorical variables.

Primary and continuous outcome variables (bowel urgency score, FBG, PG2h, FINS, C-peptide, HOMA-IR, ISI, GA, serum IL-6/IL-10/TNF-α, GLP-1, 5-HT, D-lactate, diamine oxidase, and fecal bile acids) will be analyzed using linear mixed-effects models (fixed effects: group, time, interaction; random effect: participant), reporting least-squares means with 95% *CI*. The exact mathematical formulas and covariance structures for these linear mixed-effects models will be fully reported in the final trial publication. Categorical outcomes are analyzed via χ^2^ or Fisher's exact test.

A Multiple Imputation (MI) model will be used as the primary method for missing data. The imputation model will include all primary and secondary outcomes, plus baseline covariates (age, sex, duration of diabetes, baseline metformin dose, baseline Metformin Symptom Severity Score score), with 20 Markov Chain Monte Carlo iterations to generate 20 imputed datasets. The pre-specified linear mixed-effects model will be performed on each dataset, with results pooled via Rubin's rules (Heymans and Twisk, 2022).

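### The printed HOMA-IR formula divides by 225, which fits no standard unit pair; with glucose in mmol/L and insulin in µU/mL the divisor is 22.5, so values computed as printed would be one tenth of the correct ones

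*Protocol article*

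**What the plan says.** Section 2.7.3.3 (Glucose and insulin metabolism parameters) lists "fasting insulin (FINS), HOMA-IR, and insulin sensitivity index (ISI") among the secondary outcomes and gives the formulas "HOMA-IR = (FBG × FINS)/225; ISI = 1/(FBG × FINS"). No units stand beside them, and no other part of the article gives a different divisor.

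The article's working unit for fasting glucose is mmol/L: in section 2.6.1 metformin titration is "guided by fasting blood glucose (target 4.4–7.0 mmol/L"). The unit mg/dl appears only in the diagnostic criteria of section 2.3.1, paired with mmol/L, as in "Fasting plasma glucose (FPG) ≥ 126 mg/dl (7.0 mmol/L"). The insulin unit is stated neither in section 2.7.3.3 nor in section 2.7.3.5, where fasting insulin is listed again.

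Section 2.10 (Statistical methods) names both indices in its list of continuous outcomes for linear mixed-effects models, "FBG, PG2h, FINS, C-peptide, HOMA-IR, ISI, GA, serum IL-6/IL-10/TNF-α", with results given by "reporting least-squares means with 95"% confidence intervals.

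**The concern.** HOMA-IR is a normalised index. Its divisor is the product of a reference glucose and a reference insulin, chosen so that the index equals 1 at that reference point. The divisor is therefore part of the definition, and it must match the units of the two inputs. The printed 225 looks like 22.5 with the decimal point lost.

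The scale matters because section 2.10 reports means and confidence limits in the units of the index. With the printed divisor, patients with type 2 diabetes would appear well below the reference value of 1. Readers could not set the results beside other HOMA-IR data, and anyone who took over the raw mean, SD or difference would take over the scale error too.

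A second, smaller matter is that the two printed formulas use the same product of glucose and insulin, once directly and once inverted. A reader who sees both move may take this as two pieces of support when there is one.

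**Working it through.** **Inputs.** From the article: the divisor 225 and the ISI formula (section 2.7.3.3); fasting glucose in mmol/L (section 2.6.1); 126 mg/dl = 7.0 mmol/L (section 2.3.1), so 126/7.0 = 18 mg/dl per mmol/L. Assumed, because the article does not give them: the standard HOMA-IR reference point of 4.5 mmol/L and 5 µU/mL; insulin in µU/mL; and, for the variants, 6.0 to 6.945 pmol/L per µU/mL.

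**Step 1: the divisor required by each unit pair.** The base case is 4.5 × 5 = 22.5. The other rows multiply this by the unit conversions. The last column is the required divisor over 225, that is, the printed result as a multiple of the correct one.

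| Glucose | Insulin | Required divisor | Printed / correct |
|---|---|---|---|
| mmol/L | µU/mL | 22.5 | 0.10 |
| mg/dl | µU/mL | 22.5 × 18 = 405 | 1.8 |
| mmol/L | pmol/L | 22.5 × 6.0 to 6.945 = 135 to 156 | 0.60 to 0.69 |
| mg/dl | pmol/L | 22.5 × 18 × 6.0 to 6.945 = 2430 to 2813 | 10.8 to 12.5 |

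No row gives 225.

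**Step 2: size of the error with mmol/L and µU/mL.**

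| FBG | Insulin | As printed (/225) | With 22.5 |
|---|---|---|---|
| 4.5 | 5 | 22.5/225 = 0.10 | 1.00 |
| 7.0 | 10 | 70/225 = 0.311 | 3.11 |
| 8 | 10 | 80/225 = 0.356 | 3.56 |
| 11.1 | 20 | 222/225 = 0.987 | 9.87 |

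The ratio is exactly 0.1 for every participant, so means, SDs, confidence limits and absolute differences all shrink by the same factor.

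**Step 3: what does not change.** A constant factor cancels in a t statistic and in a difference divided by its SD. As a check, 60 glucose–insulin pairs were simulated (lognormal, medians 7.5 mmol/L and 10 µU/mL, log-scale SDs 0.2 and 0.5, split 30/30 with no true effect). The HOMA-IR p-value was 0.477 with either divisor, while the mean difference went from −0.029 to −0.290.

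**Step 4: HOMA-IR and ISI.** From the printed formulas, HOMA-IR × ISI = 1/225 = 0.00444 for every participant; with the corrected divisor the product is 1/22.5 = 0.0444. Either way ISI is a constant divided by HOMA-IR. In the same simulated data the rank correlation was −1. On the log scale the two indices gave the same p-value (0.686). On the raw scale the p-values differed (0.477 for HOMA-IR, 0.911 for ISI), although both indices carry the same information.

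**The case against.** Four points can be made on the other side.

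**The tenfold error is conditional.** It needs insulin in µU/mL, which the article does not state, and it needs the analysts to apply the formula literally. A decimal point may simply have been lost when the article was prepared, with the correct formula in use at the site. This stands as a limit on the size of the error, but does not rescue 225, which is wrong for every unit pair tried. Loss in text extraction is unlikely, because decimals survive elsewhere, for example in the fasting glucose target.

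**The harm is limited.** A reader might infer that tests would be invalid, or that HOMA-IR data from this pilot would be useless for planning the next trial. The documents do not support that. Tests, p-values and standardised effects are unaffected, and a sample size computed from difference over SD does not depend on scale. Section 2.4 bases planning on the SD of the Metformin Symptom Severity Score and plans no formal efficacy testing. HOMA-IR plays no part in eligibility, metformin titration or safety assessment. Glucose and insulin are outcomes in their own right, so the index can be recomputed at any time. All of this stands.

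**The ISI formula is not an error.** Reporting an index beside its reciprocal is redundant, not wrong. A reader might infer that the plan counts the two as separate findings, but nothing in the article says so. This stands.

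**Transformation is not addressed.** A reader might infer that both indices will be modelled untransformed and that one of them must then violate normality. Section 2.10 says nothing on transformation either way and defers the exact model formulas; such detail commonly sits in an analysis plan that is not shown. With modest relative spread, a variable and its reciprocal can both be roughly symmetric. This criticism is therefore not made here.

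**Conclusion.** The HOMA-IR formula is wrong as printed and needs correcting. Given the standard definition of the index, that conclusion does not depend on which of the usual units is used. The tenfold size rests on three assumptions: fasting glucose in mmol/L, which the article supports; insulin in µU/mL, which it leaves unstated; and the formula being applied as written.

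The damage is to the absolute scale of one derived secondary outcome and to its comparability with published values. It does not reach the primary outcome or the between-group inference on HOMA-IR. The reciprocal relation with ISI is exact and worth a sentence in the report, as a caution on interpretation.

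**What to change.** In section 2.7.3.3, replace 225 by 22.5 and state the units beside the formula: FBG in mmol/L, insulin in µU/mL. If the laboratory reports insulin in pmol/L, convert it first, or print the divisor that matches and name the conversion factor. Make the same check in the full protocol and the analysis code. If the code already uses 22.5, the article still needs the correction so that the published formula and the results agree.

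Add one sentence saying that ISI is the reciprocal of HOMA-IR up to a constant and is not independent support for an effect. Optionally, analyse HOMA-IR on the log scale, where ISI gives the same result with the sign reversed, or drop ISI. Dropping it would change the named outcome set and would have to be recorded as an amendment.

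The required change is one decimal point and two units. It needs no additional data, visits or participants.

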##### Serum inflammatory markers

2.7.3.4

Serum cytokines (IL-6, IL-10, TNF-α) reflect systemic inflammation. Fasting venous blood (3–5 ml) is centrifuged at 3,500 rpm for 10 min to isolate serum and stored at −80 °C. ELISA is used for detection with *R*^2^ ≥ 0.99 for linearity. Coefficient of variation for replicate samples < 15%, and control results must meet kit specifications. Assessment at baseline and Week 2.

##### Gastrointestinal function and metabolic serum markers

2.7.3.5

Markers include GLP-1, bile acids, 5-HT, D-lactate, diamine oxidase, and fasting insulin. Sample collection and processing follow the same protocol as inflammatory markers. ELISA is used with identical quality control and optical density requirements. Assessment at baseline and Week 2.

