Mechanistically, metformin-related GI AEs center on drug–gut interactions. Oral bioavailability of metformin is only ~50–60%, yet its antihyperglycaemic effects often exceed those of intravenous administration (Stepensky et al., 2002), and intestinal mucosal concentrations are markedly higher than plasma levels (Bailey et al., 1994; Mccreight et al., 2016)—all indicating that the gut is a principal site of action. Metformin stimulates L-cell secretion of glucagon-like peptide-1 (GLP-1) and may weakly inhibit dipeptidyl peptidase-4 (DPP-4), thereby increasing active GLP-1; elevated GLP-1 can delay gastric emptying and alter intestinal transit (Migoya et al., 2010). Structurally similar to certain 5-HT3 receptor agonists, metformin can promote enterochromaffin 5-hydroxytryptamine (5-HT) release and may impair 5-HT uptake by inhibiting organic cation transporters (OCT1, OCT3) and the serotonin transporter (SERT), leading to increased 5-HT availability and altered gut motility (Yee et al., 2015; Mawe and Hoffman, 2013). Metformin also perturbs bile acid handling by reducing intestinal bile salt hydrolase activity and increasing ileal bile flow, which can impair bile acid reabsorption and, through bile acid–microbiota interactions, further modulate GLP-1 secretion (Carter et al., 2003; Beysen et al., 2012). Additionally, the gut is a major site of lactate production; metformin raises intestinal lactate concentrations [confirmed in human jejunal biopsies (Mccreight et al., 2016)] and inhibits hepatic mitochondrial glycerol-3-phosphate dehydrogenase, reducing lactate clearance and promoting local accumulation that may directly irritate the mucosa (Bailey et al., 1992; Madiraju et al., 2014). Reduced OCT1 activity or genetic polymorphisms can increase intraluminal metformin accumulation, exacerbate anaerobic metabolism, and augment lactate generation (Singh et al., 2023; Dujic et al., 2016). Barrier dysfunction and ensuing inflammatory mediators, together with altered levels of GLP-1, 5-HT, IL-6, IL-10, TNF-α, D-lactate, diamine oxidase (DAO), and bile acids, contribute to dysbiosis—reported increases in taxa such as Akkermansia spp. and certain γ-Proteobacteria have been observed in T2DM patients (Shin et al., 2014)—and dysbiosis may in turn promote symptomatology by increasing pathogenic factor release and disrupting bile-acid metabolism (Ramos et al., 2016).

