Given the multifactorial mechanisms underlying metformin-induced GI AEs, taVNS may exert therapeutic effects through multiple converging pathways: modulation of the gut microbiota (e.g., reduction of certain opportunistic taxa) and bile-acid metabolism (Zhang et al., 2025); down-regulation of proinflammatory cytokines such as TNF-α and IL-6 via vagal-cholinergic anti-inflammatory signaling (Zhao et al., 2025); bidirectional regulation of 5-HT and GLP-1 to counteract metformin-induced elevations (Yang et al., 2026); and reduction of serum D-lactate levels with consequent improvement of mucosal barrier function (Seitz et al., 2022). Importantly, taVNS may also enhance vagal efferent activity and physiologic GLP-1 secretion, thereby complementing metformin's insulin-sensitizing actions and supporting improved glycaemic management (Yee et al., 2015).

It should be emphasized that traditional ear-acupoint localization (for example, spleen and colon regions in auricular acupuncture) provides historical and anatomical rationale for stimulation site selection, but mechanistic validation requires imaging, electrophysiological, and molecular evidence. Overall, taVNS presents a testable mechanistic hypothesis to resolve the “enhance-efficacy/reduce-toxicity” dilemma of metformin and merits systematic evaluation in randomized clinical and translational studies.

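### GLP-1 and 5-HT go through the cytokine serum procedure: serum 5-HT will mainly show platelet content, and active GLP-1, if that is the form assayed, is unprotected from DPP-4

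*Protocol article*

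**What the plan says.** Section 2.7.3.5 of the protocol article sets the panel: "Markers include GLP-1, bile acids, 5-HT, D-lactate, diamine oxidase, and fasting insulin". It then gives the handling in one sentence, "Sample collection and processing follow the same protocol as inflammatory markers", and the assay in another, "ELISA is used with identical quality control and optical density requirements". The procedure it points to is in section 2.7.3.4: "Fasting venous blood (3–5 ml) is centrifuged at 3,500 rpm for 10 min to isolate serum and stored at −80 °C". Sections 2.6.5 and 2.7.3 add short-term holding at 4 °C. They leave the time limits to an SOP and the assay methods to an appendix, and require kit instructions to be followed.

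The Introduction explains why the two markers are measured. On GLP-1, metformin "may weakly inhibit dipeptidyl peptidase-4 (DPP-4), thereby increasing active GLP-1". On 5-HT, metformin may impair uptake by "inhibiting organic cation transporters (OCT1, OCT3) and the serotonin transporter (SERT), leading to increased 5-HT availability". For the intervention itself, the Introduction proposes two-way modulation of both markers, and adds that "taVNS may also enhance vagal efferent activity and physiologic GLP-1 secretion".

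**The concern.** One handling rule, suitable for cytokines, is applied to two analytes whose measured value depends on the tube and the processing. The article names the enzyme that controls active GLP-1, then specifies a sample with no stated protection against it. It also bases its 5-HT rationale on availability outside cells, then specifies a specimen that forms by clotting.

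The abstract lists helping to select biomarkers for later confirmatory trials among the pilot's products. If the specimen reflects the wrong compartment, or loses signal to an extent that varies with bench time, a marker could be dropped or kept for reasons unrelated to vagal stimulation. Stored serum cannot later be turned into platelet-poor or inhibitor-treated plasma, so the choice has to be right when the blood is drawn.

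**Working it through.** No sample-size or error-rate arithmetic applies. The check sets the stated specimen beside the stated rationale.

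**Laboratory facts used.** The documents do not state these; they are general laboratory knowledge. (i) Serum is what remains after blood has clotted. (ii) Clotting platelets release their stored 5-HT. (iii) DPP-4 stays active in drawn blood unless it is inhibited.

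**5-HT.**
- Quantity in the rationale: enterochromaffin release and availability after impaired uptake (Introduction).
- Specimen: serum, handled as for the cytokines (2.7.3.4 and 2.7.3.5).
- By (i) and (ii), the assay reads free 5-HT plus the platelet store, and the store dominates. The specimen does not match the rationale, whichever ELISA kit is used.

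**GLP-1.**
- Quantity in the rationale: active GLP-1 for the metformin mechanism, and GLP-1 secretion for the taVNS mechanism (Introduction).
- Quantity assayed: listed only as GLP-1, with neither active nor total stated (2.7.3.5).
- If active, then by (iii) the result also depends on time to processing and on the DPP-4 activity in that tube.
- If total, it speaks to secretion and depends much less on DPP-4 protection. The GLP-1 half of the point is therefore conditional.

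**Does deferred detail remove the problem?** Section 2.6.5 leaves assay methods, quality control and batches to the appendix, and section 2.7.3 requires kit instructions to be followed. Neither withdraws the serum specimen fixed in 2.7.3.4 and 2.7.3.5. An appendix calling for plasma or inhibitor tubes would contradict those sections, and they would still need correcting.

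**Effect on the comparison.** Both arms follow the same procedure, so the expected result is added variance and attenuation, not a shift between arms. The primary outcome is a questionnaire score and uses no blood sample.

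**Number of samples.**
- Section 2.7.3.5 gives baseline and Week 2: 60 participants × 2 = up to 120 samples per marker.
- Table 1 marks GLP-1 and 5-HT at Week 2 only: 60 × 1 = up to 60.
- Section 2.6.5 speaks of baseline, Week 2 and Week 4 for selected markers, with some repeated at baseline and one later visit.
- Section 2.10 analyses both markers in a mixed model with group, time and their interaction. That needs at least two time points per marker, so on the Table 1 schedule the time and interaction terms could not be estimated.

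**Size of the error.** The documents give no degradation rate, clotting time, assay recovery, platelet share or marker SD, so the size cannot be computed from them.

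**The case against.** The strongest case against is that this is laboratory detail which an article leaves to its appendix, SOP and kit inserts. That stands for additives, chilling and time limits taken alone. It does not stand for the specimen, because the article positively says serum and positively says the same procedure. Two further points also stand: these are secondary markers, and the pilot plans no formal efficacy test (section 2.4).

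A reader might infer more than the documents support:

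- *That neither marker can measure what the hypothesis concerns.* This is too strong for GLP-1, since the form is unstated and the taVNS rationale includes secretion, for which total GLP-1 is informative. Serum 5-HT may also still carry some information on release.
- *That serum 5-HT will move opposite to the hypothesis*, because blocking SERT empties platelets while raising free 5-HT. The SERT statement describes metformin, which both arms receive. The article does not say that taVNS acts on SERT.
- *That a definite share of active GLP-1 is lost.* With fraction remaining = 2^(−t/h), assumed half-lives h of 4 h and 1 h, and assumed clotting times t of 0.5 h and 1 h, the remainder runs from 2^(−0.125) = 0.92 to 2^(−1) = 0.50, a loss of 8% to 50%. All the inputs are assumptions, so the range illustrates dependence on handling and does not estimate this trial's error.
- *That the between-group comparison is biased.* Metformin is titrated and DPP-4 inhibitors may be added (section 2.6.1), so in-tube DPP-4 activity could come to differ by arm. The documents give no basis for the direction or size of this. A permitted DPP-4 inhibitor also changes circulating active GLP-1, which no tube corrects.

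**Conclusion.** The point holds as a mismatch between specimen and rationale for two secondary mechanistic markers. It is firm for 5-HT: serum will mainly report platelet 5-HT. It is conditional for GLP-1: it applies if the active form is assayed. The consequence is noise, attenuation and results that are hard to interpret when biomarkers are chosen for the next trial. The primary symptom score is untouched, and no bias between arms is shown.

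The conclusion rests on the three laboratory facts listed in the working and on reading the same-procedure sentence literally. The number of samples affected is up to 120 or up to 60 per marker, depending on whether section 2.7.3.5 or Table 1 is followed. The change is worth making before samples are taken because it is cheap then and cannot be made in full afterwards.

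**What to change.** Replace the blanket handling sentence in section 2.7.3.5 for these two analytes.

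- **GLP-1:** at the scheduled draws, collect into a chilled anticoagulant tube with a DPP-4 inhibitor, with a fixed maximum time to spin and to freeze. State whether the assay reads active or total GLP-1.
- **5-HT:** measure in platelet-poor plasma, again with fixed times to spin and freeze.
- **If serum is kept, or has already been collected:** assay total GLP-1 only, report the other result as *serum (mainly platelet) 5-HT*, and make no claim about active GLP-1 or 5-HT availability.
- **Schedule:** reconcile section 2.7.3.5 (baseline and Week 2), section 2.6.5 and Table 1 (Week 2 only), so that a baseline sample is taken and the mixed model in section 2.10 can be fitted.

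The cost is one more tube type at a scheduled draw and an SOP change. If Table 1 reflects current practice, a baseline sample for these markers has to be added as well. Keeping serum costs nothing at the bench but narrows what the pilot can say about either marker.
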